## Analysis plan

The primary analysis will be a mixed model regression to take into account the three repeated measures of platelet function at 1, 2 and 24 hours after completion of PPCI. Platelet function on arrival at the hospital, and platelet function after completion of PPCI, are not expected to be influenced by door-to-balloon time and will be entered as covariates. Other potential confounding factors influencing platelet function (e.g. peak troponin, age, gender, diabetic status) will also be entered as covariates. Two key predictors will be tested in the model, namely the effects of (a) door-to-balloon time and (b) platelet function on arrival at the hospital.

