# Lay Summary

Heart attacks are increasingly being treated with immediate re-opening and placement of a metal-mesh tube (stent) in the blocked heart artery. In addition to scaffolding the artery with a stent, drugs are used to thin the patient’s blood. We have recently changed the drugs given to patients presenting to the Bristol Heart Institute with heart attacks. The drugs we have selected are potent blood thinners and have been shown to act very fast.

In this study we want to measure the level of blood thinning achieved at the end of the stenting procedure. We believe that there may be a variable response to the blood thinning drugs and patients with a low response may be at increased risk of blood clotting problems. We will describe the relationship between the measure of blood thinning at the end of the procedure with the time given for the drug to take effect and ultimately with complications developed within the first 30 days following the stenting procedure.

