The newly amended BHI anti-thrombotic protocol assumes that all STEMI patients will achieve adequate platelet inhibition with prasugrel by the time bivalirudin is stopped, immediately after treatment with a coronary stent. The validation of this assumption in’real’ STEMI patients has not been tested. This is the aim of the study.

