# Hypothesis and Study Objectives

Minimising the time from STEMI symptom onset to definitive treatment, with mechanical revascularisation, remains a major focus of attention in optimising the PPCI service. We hypothesise that continued reductions in the “door to balloon” time (time from hospital admission to achieving an open artery in the catheter laboratory) may result in some patients undergoing PPCI with incomplete P2Y12 blockade, leading to an increase in risk of early thrombotic events. We speculate that the rapid restoration of coronary flow achieved with PPCI may offer inadequate time to achieve platelet inhibition with prasugrel, prior to the loss of the anti-thrombin effect of bivalirudin.

The primary objective of the study is to describe variation in platelet activity at the end of the PPCI and to quantify the relationship between “door to balloon time” and platelet function in the first 24 hours after completing the PPCI.

The secondary objective of the study is to test the hypothesis that patients with high platelet activity at the time of arrival at hospital (baseline) achieve less platelet inhibition in the first 24 hours following commencement of anti-thrombotic and anti-platelet therapy.

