### Confounding variables

We will measure and record confounding variables associated with the characteristics of the index MI and platelet reactivity. Variables will include: timing of symptoms/presentation relative to initiation of treatment, the maximum CKMB/Troponin T, age, gender, co-existent diabetes, concomitant treatments, high sensitivity CRP and WCC.

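### The primary model adjusts for end-of-PPCI platelet function on the ground that door-to-balloon time does not affect it, which contradicts the study's own hypothesis and can remove part of the effect being tested

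*Protocol*

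**What the plan says.** Protocol 7.6 (Analysis plan) specifies a mixed model with three repeated outcomes, at 1, 2 and 24 hours after PPCI. Two key predictors are tested: door-to-balloon time and platelet function on arrival. The arrival value and the end-of-PPCI value (Time 1 in the schema) are both covariates, and the reason given is that the arrival value and "platelet function after completion of PPCI, are not expected to be influenced by door-to-balloon time and will be entered as covariates". The same section adds: "Other potential confounding factors influencing platelet function (e.g. peak troponin, age, gender, diabetic status) will also be entered as covariates".

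Other sections treat the end of PPCI differently:

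- Section 6 (Hypothesis): shorter door-to-balloon times "may result in some patients undergoing PPCI with incomplete P2Y12 blockade, leading to an increase in risk of early thrombotic events".
- Section 5 (Background): prasugrel is given on arrival, before angiography. The assumption that the study sets out to test is that "all STEMI patients will achieve adequate platelet inhibition with prasugrel by the time bivalirudin is stopped", which is the Time 1 moment.
- Section 4 (Lay Summary): one stated purpose is to report "the relationship between the measure of blood thinning at the end of the procedure with the time given for the drug to take effect".
- Section 7.3.1 (Primary Outcomes): completion of PPCI is one of the assessment times of the primary outcome. The change in profile is to be tested through the interaction of door-to-balloon time with time after PPCI.

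**The concern.** Because prasugrel is given on arrival, door-to-balloon time is part of the time that the drug has had to work when Time 1 is sampled. The hypothesis says that this time matters. The analysis plan says that it does not, and uses that statement to justify conditioning on Time 1.

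If the hypothesis is true, Time 1 is an intermediate variable. The door-to-balloon coefficient then describes only the part of the effect at 1 to 24 hours that Time 1 does not already reflect. The same holds for the second key predictor: any influence of arrival platelet function that shows by the end of PPCI is also taken out. In addition, a time point listed in the primary outcome drops out of the modelled outcomes.

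What is at stake is the reading of a null result. It could be reported as showing that faster PPCI does not cost platelet inhibition, when the adjustment itself may have produced it.

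**Working it through.** **1. Plan's own figures.** The protocol gives no expected door-to-balloon effect at Time 1 and no correlation of Time 1 with later values, so there is no figure of its own to reproduce on this point. The nearest input is in section 7.5: correlations of 0.5 to 0.8 among the repeated measures, with relative efficiency 1.25 to 1.50. Under a common correlation the relative efficiency for three measures is 3/(1 + 2·rho): 1.50 at 0.5, 1.25 at 0.7 and 1.15 at 0.8. The last step, 135/1.25 = 108, is correct arithmetic. The 135 itself was not reproduced: a partial F test with f² = 0.05/0.75 = 0.0667, one of eight predictors tested, alpha 0.025 and 80% power gives 146. That is a separate matter, and nothing below depends on it.

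**2. Effect of the adjustment.** Let b_1 be the door-to-balloon effect on Time 1 and b_L its effect on the later values. Let rho be the correlation of Time 1 with later values given door-to-balloon time and the other covariates. With equal variances, the slope of a later value on Time 1 is rho, so

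adjusted coefficient = b_L − rho·b_1.

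With k = b_1/b_L, the share retained is 1 − rho·k and the share removed is rho·k.

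**3. Numbers.** Share of the door-to-balloon effect removed:

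| rho | k = 0 | k = 0.5 | k = 1 | k = 1.5 |
|---|---|---|---|---|
| 0.3 | 0% | 15% | 30% | 45% |
| 0.5 | 0% | 25% | 50% | 75% |
| 0.7 | 0% | 35% | 70% | 105% |
| 0.8 | 0% | 40% | 80% | 120% |

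The column k = 0 is the analysis plan's stated expectation. Any k above 0 follows the hypothesis. A share above 100% means that the coefficient changes sign, which needs rho·k above 1, i.e. an effect that is larger at the end of PPCI and fades.

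**4. Check by simulation.** In 400,000 simulated patients with the same effect at all four times (k = 1), the coefficient fell from 0.2584 to 0.1295 at rho = 0.5 (retained 0.50) and from 0.2606 to 0.0529 at rho = 0.8 (retained 0.20). Both agree with 1 − rho.

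**5. Interpretation.** In that simulation the correlation comes only from stable differences between patients, not from Time 1 acting on later values, and the attenuation still occurs. The remainder is therefore not automatically a clean direct effect.

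**The case against.** The strongest reply is that the size is unknown, and that stands. A reader might infer that most of the effect is lost. That needs rho·k above 0.5, and the protocol fixes neither term. The 0.5 to 0.8 range in section 7.5 refers to the repeated measures, which are those at 1, 2 and 24 hours, and not to Time 1. The planning R-squared values even point lower: if Time 1 is among the eight predictors, a reduced-model R-squared of 0.20 limits its correlation with a later value to about √0.20 = 0.447, so the loss would be about 45% at k = 1 and 22% at k = 0.5. Conversely, correlations of 0.5 to 0.8 would give Time 1 alone an R-squared of 0.25 to 0.64, which does not fit 0.20.

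A reader might also infer that the effect must be greatest at Time 1. The protocol does not say so: Background places the possible gap in protection in the period when bivalirudin wanes. Nor can the loss be turned into the trial's power, because section 7.5 powers an increment over the other covariates and not a total effect.

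A further reply is that the announced door-to-balloon-by-time interaction escapes the problem. This is partly right. With complete data, a covariate that is constant within a patient leaves the contrasts between 1, 2 and 24 hours unchanged. But section 7.6 names the effect of door-to-balloon time as the tested predictor, and an effect that is the same at all three times lies wholly in that main effect.

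Finally, one may want to know how platelet function develops after PPCI given its level at the end. That is a legitimate question, but a secondary one.

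**Conclusion.** The contradiction is established from the text alone: the reason given for adjusting for Time 1 conflicts with sections 4, 5 and 6, and the adjustment takes a listed time point of the primary outcome out of the modelled outcomes. If the hypothesis is true, the main effects of both key predictors exclude what is already present at the end of PPCI.

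The size is conditional. Part of the door-to-balloon effect is removed, possibly most of it: rho·k, assuming equal variances and values of rho and k that the protocol does not supply. It is zero if k = 0. The choice is lopsided: if k = 0, dropping the covariate costs only precision; if k is above 0, keeping it distorts the primary estimate. Because section 7.6 fixes both the covariate and its rationale, this is not a detail left to the SAP, and it should be corrected before the analysis.

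Peak troponin is a lesser point that rests on inference. Section 7.3.3 records "the maximum CKMB/Troponin T", and a maximum can arise after the balloon, so it may be a post-exposure variable. A reader might infer that the hypothesis itself says door-to-balloon time affects troponin. It does not mention troponin, and the protocol lists it only as a confounder.

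**What to change.** 1. In section 7.6, delete the statement that end-of-PPCI platelet function is not expected to depend on door-to-balloon time.
2. Take Time 1 out of the covariates of the primary model and add it to the repeated outcomes (end of PPCI, 1, 2 and 24 hours). Use time as a category, with the door-to-balloon-by-time interaction announced in section 7.3.1. Adjust for arrival platelet function and pre-exposure covariates such as age, gender and diabetic status.
3. State which door-to-balloon contrast carries the 0.025 test, since section 7.5 assumes one tested predictor.
4. Keep the Time 1-adjusted model as a labelled secondary (mediation) analysis with its assumptions stated, and put the troponin-adjusted model among the sensitivity analyses.

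Cost: no new samples, as Time 1 is already collected. Some precision gained from the Time 1 covariate is lost, partly offset by a fourth repeated measure. The three-measure wording and the relative-efficiency step in section 7.5 must be brought into line.

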## Outcomes

### Primary Outcomes

The primary outcome for study is the platelet function assessment measured in peripheral ‘whole’ blood. Functional assessment of ADP receptor, arachidonic acid pathway, and thrombin related platelet activation will be measured using a multiple electrode analyser (MEA – Multiplate platelet function analysis).

Platelet function (measured in peripheral ‘whole’ blood, see above) will be assessed on arrival at hospital, at completion of the PPCI, 1, 2 and 24 hours after the completion of the PPCI. These measurements will allow the study to test how the profile of platelet function changes over the period of time in which the effect of bivalirudin wanes and prasugrel increases, by assessing the interaction between door-to-balloon time and time-after-completion of PPCI.

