## Sample size and justification

The primary analysis will be a mixed model regression (see below). Calculation of the sample size needed to detect a statistically significant effect of a key predictors in such analyses require the following assumptions to be defined (parameter = estimate):

r-squared for full model = 0.25

r-squared for reduced model (excluding key predictor) = 0.20

number of predictors in full model = 8

number of predictors being tested = 1

Because two key predictors will be tested (see below), a significance level of 0.025 will be adopted (Bonferroni correction) giving a nominal hypothesis test at p<0.05 for each predictor. For 80% power, the above assumptions require a target sample size of 135. This target sample size needs to be further adjusted by the relative efficiency of the analysis, i.e. to take into account the three repeated measures. Estimating the relative efficiency requires further assumptions about the correlations between the repeated measures; for correlations ranging from 0.5 to 0.8, the relative efficiency varies from 1.25 to 1.50. Taking the lower estimate of relative efficiency gives a final target sample size of 108 (i.e. 135/1.25).

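### The primary outcome section promises a test of the door-to-balloon by time interaction, but the primary analysis and sample size provide only one pooled door-to-balloon effect

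*Protocol*

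**What the plan says.** Section 7.3.1 (Primary Outcomes) lists samples on arrival, at the end of PPCI, and 1, 2 and 24 h later. It says they allow a test of how the profile changes while bivalirudin wears off and prasugrel takes hold, "by assessing the interaction between door-to-balloon time and time-after-completion of PPCI".

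Section 7.6 (Analysis plan) specifies a mixed model for "the three repeated measures of platelet function at 1, 2 and 24 hours after completion of PPCI". The arrival and end-of-PPCI values "are not expected to be influenced by door-to-balloon time and will be entered as covariates". It then states: "Two key predictors will be tested in the model, namely the effects of (a) door-to-balloon time", the second being arrival platelet function. No interaction with time is mentioned.

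Section 7.5 (Sample size and justification) assumes "number of predictors in full model = 8" and "number of predictors being tested = 1", with R-squared 0.25 against 0.20, alpha 0.025 and 80% power, giving 135. It continues: "This target sample size needs to be further adjusted by the relative efficiency of the analysis". Dividing by 1.25 gives 108.

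Section 6 words the primary objective as the relationship between door-to-balloon time and platelet function over the first 24 h after PPCI. Its hypothesis, and the Background, concern a gap soon after bivalirudin stops.

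**The concern.** Section 7.3.1 asks whether the door-to-balloon slope differs between sampling times. Sections 7.5 and 7.6 test whether one common slope is zero. These are different hypotheses. With three times and time as a category, the interaction has 2 degrees of freedom; the sizing covers 1. A statistician working from 7.3.1 and one working from 7.6 would report different primary results from the same data, and 108 is justified for only one of them.

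A second issue is conditional. The mechanism described is an early one: bivalirudin wanes quickly while prasugrel may not yet be fully active. If differences in door-to-balloon time matter at 1 and 2 h but little at 24 h, the 24 h sample pulls the pooled slope towards zero. A real early effect could then be missed.

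**Working it through.** **Inputs from section 7.5.** f² = (0.25 − 0.20)/(1 − 0.25) = 0.0667; 8 predictors; 1 tested; alpha 0.025; N = 108; correlations (ρ) 0.5 to 0.8.

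**Assumptions not in the protocol.** Compound symmetry, and the relative effect at 1, 2 and 24 h, taken as (1,1,1), (1,1,0.5) or (1,1,0).

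**The plan's own figures.**
- 135/1.25 = 108 is correct arithmetic.
- The usual F test for an R-squared increase (noncentrality f²N, N − 9 error df) needs 146 for 80% power, not 135; at 135 the power is 76.7%.
- The relative efficiency of a mean of three measures is 3/(1 + 2ρ): 1.50 at ρ = 0.5, 1.25 at 0.7 and 1.154 at 0.8. The stated 1.25 therefore belongs to ρ = 0.7, not 0.8.

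These two discrepancies are separate from this point. The second does show which test was sized: 1.50 and 1.25 are values of the formula for one effect common to all three times.

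**Pooled test.** With mean relative effect m, efficiency against a single measurement is m² × 3/(1 + 2ρ). Noncentrality is 108 × 0.0667 × efficiency = 7.2 × efficiency, on 1 and 108 − 8 − 1 = 99 df.

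**Contrast on the 1 h and 2 h samples.** With equal effects at both times, efficiency is 2/(1 + ρ) = 1.333, 1.176 and 1.111 at ρ = 0.5, 0.7 and 0.8.

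Worked case, no effect at 24 h and ρ = 0.5: m = 2/3; pooled efficiency = 0.444 × 1.5 = 0.667; noncentrality 4.8; power 46.9%. The early contrast has noncentrality 7.2 × 1.333 = 9.6 and power 79.3%.

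| Effect at 1, 2, 24 h | m | Pooled efficiency (ρ 0.5/0.7/0.8) | Pooled power | 1–2 h contrast power | 2-df interaction power |
|---|---|---|---|---|---|
| 1, 1, 1 | 1 | 1.50/1.25/1.15 | 84/76/73% | 79/74/71% | 2.5% (the alpha) |
| 1, 1, 0.5 | 0.833 | 1.04/0.87/0.80 | 68/59/55% | 79/74/71% | 18/30/46% |
| 1, 1, 0 | 0.667 | 0.67/0.56/0.51 | 47/40/37% | 79/74/71% | 70/92/99% |

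The interaction column uses noncentrality 7.2 × Σ(bₜ − m)²/(1 − ρ) on 2 and 198 df, where bₜ is the relative effect at time t.

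Compared with pooling, the 1–2 h contrast gives up about 2 to 5 points if the effect is constant and gains about 32 to 34 if it has gone by 24 h. It is not proof against a steeper decline: with an effect at 1 h only, its power is 24/21/20% and the pooled test's is 12/11/10%.

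**Adding the end-of-PPCI sample to an early contrast.** Section 7.6 expects that value not to depend on door-to-balloon time. On that assumption the pattern over end of PPCI, 1 h and 2 h is (0,1,1), so m is again 2/3 and power is again 47/40/37%. Such a contrast would carry the same dilution.

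**The case against.** The strongest reply is that the pooled effect is a legitimate target. The primary objective in section 6 speaks of the first 24 h as a whole, and one slope over 1, 2 and 24 h is a fair reading of it. If the effect persists, pooling is the most efficient of the tests compared. If the R-squared gain of 0.05 was meant for the pooled effect, there is no loss against plan. Section 9 also defers detail to a statistical analysis plan, and 7.6 does not forbid an interaction term.

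Much of this stands. A reader might infer that the analysis definitely dilutes the effect and is underpowered. The protocol does not support that, because it gives no effect by time point and its early-gap hypothesis is only qualitative. A reader might also conclude that the interaction should simply replace the main effect. That would be a poor exchange: if the effect is constant, the interaction test rejects at only its 2.5% alpha level, and with half the effect left at 24 h it still has less power than the pooled test.

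The reply does not remove the mismatch. The tested predictors, alpha, degrees of freedom and N are fixed in the protocol itself. A later analysis plan can add a term, but the justification for 108 would still belong to another test than the one 7.3.1 describes.

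**Conclusion.** The inconsistency is established from the text and needs no assumption about time course: section 7.3.1 announces an interaction, while 7.5 and 7.6 specify and size a single door-to-balloon effect. It should be corrected, since the stated question would otherwise go untested.

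The power cost is a conditional range. It rests on compound symmetry, on f² = 0.0667 describing a single-time effect, and on an assumed pattern over time. Under these, the pooled test falls from 84–73% with a constant effect to 68–55% with half left at 24 h and 47–37% with none left. It should be reported as that range and not as a known defect.

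**What to change.** - In 7.6, include time as a category and the door-to-balloon by time interaction over 1, 2 and 24 h, and report the door-to-balloon slope with its confidence interval at each time.
- Keep the end-of-PPCI sample out of the outcome contrast for as long as it is a covariate.
- Name one primary door-to-balloon estimand. The slope over 1 h and 2 h fits the early-gap hypothesis and costs little if the effect is constant; a pooled slope is also defensible if 7.3.1 is reworded to match. Do not make the 2-df interaction the only test.
- Align section 6, 7.3.1, 7.5 and 7.6 with that choice.
- In 7.5, restate the power that 108 patients give for the chosen test, with the assumed effect at each time. If the 1–2 h slope is chosen, claim no efficiency gain from the 24 h sample.

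The cost is wording and a revised power statement. The blood samples and the data collected do not change.

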# Study Procedures

## Patient Presentation

Patients are referred with STEMI from 3 groups; direct referral from paramedics diagnosing STEMI in the community, referral from general practice or secondary care, and referral within UHBristol (i.e. from A&E or in-patient referral).

Where possible, patients are directly transferred to the catheter laboratory and angiographic assessment is undertaken following a brief clinical assessment and consent of the patient for the procedure.

## Standard Treatment of Patients

### Pre- & Peri-Procedural Care

An oral loading dose of prasugrel is administered as soon as possible, following assessment and bivalirudin is commenced at the time of the procedure. If angiography confirms the presence of a ‘culprit’ atherosclerotic lesion within the coronary arteries, immediate PPCI is undertaken. It is usual practice for bloods to be taken from the arterial sheath at the end of the procedure to assess routine haematological and chemical pathology parameters, including: haemoglobin, white cell count and differential, platelet count, urea, creatinine, eGFR, electrolytes, liver function, CRP and troponin.

### Post-procedural Inpatient Care

Following the procedure, patients are usually transferred to the coronary care unit (CCU). Secondary preventative treatment, including beta-blockade, ACE inhibition, and statin therapy, is commenced during the in-patient stay, an echocardiographic assessment of left ventricular function is obtained and contact is made with the cardiac rehabilitation team. Ideally, patients transfer from CCU to a cardiology ward at 24hrs and discharge is arranged from 48hours onwards.

